**6.2 Important steps for cohort creation**

***Cohort entry date:*** The cohort entry date is of the first claim for fluticasone-salmeterol (Advair HFA) (exposure) vs. fluticasone-salmeterol (Advair Diskus) (referent) between January 1, 2007 and November 30, 2023

***Study period:***

Baseline Period: The baseline period is defined as 180 days prior and up to and including the cohort entry date [-180, 0] unless otherwise noted in the design diagram.

Follow up Period: The follow-up period starts 1 day after the cohort entry date and continues until censoring. For further details on censoring, see section 8.2.

***Note:*** All diagnosis, procedure and generic names of drugs are given in the file named “Protocol Appendix.”

| Steps |  |
| --- | --- |
| **6.2.1** | **Patients with prescription for Advair HFA/Diskus**  *Advair HFA is the exposure and Advair Diskus is the reference* **(fills of both on cohort entry are not allowed)**  **Date of prescription is called the index date**  [assessed between January 1, 2007 and November 30,2023]  *Appendix Table 1 “Exposure definitions,” variables names: Advair HFA, Advair Diskus* |
| **6.2.2** | **Exclude patients who do not have continuous insurance enrollment during baseline period**  [assessed between 180 days prior up to and including index date (-180, 0)] |
| **6.2.3** | **Exclude patients with no prior diagnosis of COPD**  [assessed 3 years prior to and including the index date (-1095, 0)]  *Appendix Table 2 “Exclusion criteria,” variable name: Diagnosis of COPD* |
| **6.2.4** | **Exclude patients who are under the age of 40**  [assessed on the index date (0, 0)] |
| **6.2.5** | **Exclude patients who received another ICS-LABA script (besides Advair HFA or Advair Diskus)**  [assessed between 180 days prior up to and including index date (-180, 0)  *Appendix Table 2 “Exclusion criteria,” variable name: ICS-LABA besides Advair* |
| **6.2.6** | **Exclude patients who started a LAMA, LAMA-LABA, or ICS-LAMA-LABA on the cohort entry date**  [assessed on the cohort entry date (0,0)] |

1. **Covariates**

The baseline covariate assessment period for all measures will start 180 days before cohort entry and will stretch up to and include the day of cohort entry with the following exceptions: (1) We will assess age, sex, race, region, year of cohort entry, and index prescription by a pulmonologist only on the day of cohort entry; (2) We will assess the presence of any prior asthma diagnosis using all available data and stretching up to (and including) the day of cohort entry. Diagnosis based covariates will be defined using any care setting and any diagnosis position unless otherwise specified. All codes for these variables are provided in Appendix Table 3, “Covariates.” The variable names are as listed below in Table 1. All variables listed below will be included in our propensity score model. We will use a missing indicator in our propensity score model in the case that data are missing for any covariates.

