**Part 1: Background**

Fluticasone-salmeterol has long been approved for the treatment of chronic obstructive pulmonary disease (COPD). In the US, GlaxoSmithKline markets two different inhalers containing fluticasone-salmeterol: Advair Diskus (first approved in 2000) and Advair HFA (first approved in 2006). The former, a dry powder inhaler, is approved for the indications of both COPD and asthma, while the latter, a metered-dose inhaler, is only approved for the indication of asthma. However, a small randomized controlled trial showed that Advair HFA had similar efficacy to Advair Diskus when treating COPD.^1^ Yet, metered dose inhalers have also been associated with more errors than dry powder inhalers.

Given ongoing clinical uncertainty, we will analyze the comparative effectiveness and safety of fluticasone-salmeterol delivered via metered-dose inhaler (Advair HFA) vs dry powder inhaler (Advair Diskus) among patients with COPD treated in routine clinical practice. The primary effectiveness outcome will be first moderate or severe COPD exacerbation; the primary safety outcome will be first pneumonia hospitalization. Secondary outcomes will include the annual rate of total moderate or severe COPD exacerbations (analyzed separately and together), first moderate exacerbation, first severe exacerbation, and annual rate of total pneumonia hospitalizations.

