**6.1 Cohort Summary**

All patients with COPD, defined by 3 outpatient claims or 1 inpatient claim in the prior 3 years (PPV 0.82 [0.72-0.89]),^2^ who initiated a prescription for fluticasone-salmeterol (Advair HFA) (exposure) vs. fluticasone-salmeterol (Advair Diskus) (referent) between January 1, 2007 and November 30, 2023. We will require a 180-day washout period for both the exposure and the referent. We will also require 180 days of continuous insurance coverage prior to cohort entry. We will include patients who received other therapy in the baseline period (whether single-agent inhalers [ICS, LAMA, LABA], LAMA-LABAs, or triple therapy). In other words, we will include patients who may be stepping up therapy (from monotherapy), stepping down therapy (triple therapy), or switching (from LAMA-LABA). Following other studies, we will exclude patients who are less than age 40 to increase the specificity of COPD diagnoses. This will help further ensure that patients entering the cohort are receiving triple therapy for COPD rather than another respiratory condition.

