**Table 1: Patient characteristics**

| **Characteristic** |
| --- |
|  |
| **Demographics** |
| Age |
| Female |
| Race |
| Region |
| **Year of cohort entry** |
| **Baseline lung disease** |
| Moderate COPD exacerbations |
| Severe COPD exacerbations |
| Total COPD exacerbations (moderate or severe) |
| SABA fills |
| SAMA fills |
| SAMA-SABA fills |
| Pneumonia hospitalizations |
| Respiratory antibiotic fills^b^ |
| Prior diagnosis of asthma (all available data) |
| Claim for home oxygen or oxygen equipment |
| CPAP/BiPAP |
| Spirometry |
| Index prescription by pulmonologist |
| Smoking |
| Pulmonary rehabilitation |
| LAMA |
| LABA |
| ICS |
| LAMA-LABA |
| ICS-LAMA-LABA |
| Chronic azithromycin |
| Roflumilast |
| Chronic prednisone |
| **Events within 30 days of cohort entry** |
| Moderate or severe COPD exacerbations |
| Respiratory antibiotic fill^b^ |
| **Other co-morbidities** |
| Combined comorbidity index |
| Frailty score |
| Obstructive sleep apnea |
| Hypertension |
| Diabetes |
| Obesity |
| Coronary artery disease |
| Peripheral vascular disease |
| Venous thromboembolic disease (DVT or PE) |
| Congestive heart failure |
| GERD |
| Renal failure |
| Osteoporosis |
| Dementia/other neurologic disease |
| Malignancy, non-metastatic |
| Metastatic solid organ malignancy |
| Anxiety disorder |
| Depression |
| **Healthcare utilization in baseline period** |
| Emergency department visits |
| Hospitalizations |
| 90-day readmissions |
| Office visits |
| Pulmonologist visits |
| Prescription drug claims |
| BMP or CMP |
| CBC with differential ordered |
| Electrocardiogram |
| Echocardiogram |
| CT scan |
| Bronchoscopy |
| Colonoscopy |
| Mammography |
| Bone-mineral density scan |
| Influenza vaccination |
| **Non-pulmonary medications** |
| Statins |
| Beta-blockers |
| ACE-inhibitors |
| ARBs |
| Calcium channel blockers |
| Thiazide-like and thiazide-type diuretics |
| Loop diuretics |
| Proton-pump inhibitors |
| H2-receptor blockers |
| Metformin |
| Sulfonylureas |
| SGLT2 inhibitors |
| DPP-4 inhibitors |
| GLP-1 receptor agonists |
| Benzodiazepines |
| SSRIs or SNRIs |

a. Our method for identifying respiratory antibiotics is described in Appendix Table 4, “Method for identifying respiratory antibiotics.

1. Outcome variable and study follow-up
   1. Outcome variables and study follow-up:

**Primary effectiveness outcome:** First moderate or severe COPD exacerbation

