**Secondary**

1. All-cause mortality
2. Annual rate of moderate or severe COPD exacerbations
3. Annual rate of moderate COPD exacerbations
4. Annual rate of severe COPD exacerbations
5. First moderate COPD exacerbation
6. First severe COPD exacerbation
7. Annual rate of hospitalizations for pneumonia
   1. Follow up and censoring

**Primary effectiveness and safety outcomes**: Follow up starts 1 day after the cohort entry date and continues until any of the following occurs:

(1) discontinuation of index therapy (with a 60-day grace period between fills and a 60-day exposure risk window)

(2) switch from exposure to referent or vice-versa

(3) initiation of a different inhaler regimen (ICS, LABA, ICS-LABA, LAMA-LABA, ICS-LABA-LABA)

(4) death

(5) the end of insurance coverage

(6) the end of data

(7) 365 days

1. **Statistical analysis**: For our primary balancing methodology, we will perform inverse probability of treatment weighting (IPTW) with stabilized weights using propensity scores estimated from an over-identified covariate balancing propensity score (CBPS) model. We specified a logistic regression model for the CBPS estimation procedure, including the variables in Table 1 as predictors of exposure.

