| **3** | Prior diagnosis of asthma | GOLD guidelines recommend ICS-containing regimens for those with a prior diagnosis of asthma. This subgroup analysis seeks to examine the comparative effectiveness of Advair Diskus and HFA in this population where ICS-based regimens are thought to be particularly beneficial. | Addresses comparative effectiveness and safety in lower risk subgroup | None |
| **4** | Excluding patients with recent asthma diagnosis codes (in prior 3 years). | GOLD guidelines recommend ICS-containing regimens for those with a prior diagnosis of asthma. This subgroup analysis seeks to examine the comparative effectiveness of Advair Diskus and HFA in this population where ICS-based regimens are thought to be particularly beneficial. | Addresses comparative effectiveness and safety in lower risk subgroup | Low power |
| **6** | Spirometry before cohort entry | Maintenance inhalers are more likely to be effective for patients who have a proven diagnosis of COPD (as measured by spirometry). We want to examine whether, among patients with spirometry (i.e. patients most likely to benefit from inhaler therapy), there is any difference between Advair Diskus and HFA. | Addresses comparative effectiveness and safety in population enriched for COPD (closer to RCT population) | We do not know the actual measurements from the spirometry. |
| **7** | Index-prescription from a pulmonologist | Pulmonologists may be more likely to assign guideline-recommended therapy compared to other practitioners. We will examine whether Advair HFA has similar effectiveness to Advair Diskus among patients whose index prescription is from a pulmonologist. | Addresses generic quality in population enriched for patients who should be receiving guideline-concordant care. | Low power. |
| 8 | Cohort entry between 2007-2018 | This is the primary time during which Advair Diskus and Advair HFA were on the market without generic competition, limiting confounding from competing devices that patients might be alternatively prescribed. | Limits confounding from competing inhalers, providing a more direct comparison of Advair Diskus vs. HFA. | None. |

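### The primary propensity score records baseline inhaled therapy by drug class only, so in a device comparison baseline nebuliser use is neither adjusted for nor checked for balance

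*Protocol*

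**What the plan says.** In the Protocol's Covariates section the rule is "All variables listed below will be included in our propensity score model". The Statistical analysis section repeats it for the covariate balancing propensity score (CBPS), a logistic model "including the variables in Table 1 as predictors of exposure". The primary adjustment set is therefore Table 1.

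Under baseline lung disease, Table 1 has three short-acting items (SABA, SAMA and "SAMA-SABA fills") and five maintenance items (LAMA, LABA, ICS, LAMA-LABA, ICS-LAMA-LABA). All eight are drug classes. The only respiratory equipment items are home oxygen and CPAP/BiPAP. Nothing is named for nebulised fills, nebuliser equipment, spacers, or prior metered-dose or dry powder use.

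Three other statements bear on the point:

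- Section 6.1 admits people with inhaler experience: "We will include patients who received other therapy in the baseline period".
- Part 1 says that "metered dose inhalers have also been associated with more errors than dry powder inhalers".
- Subgroup analyses, row 6, concedes a gap in severity data: "We do not know the actual measurements from the spirometry".

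**The concern.** Both arms receive fluticasone-salmeterol, and only the device differs. A patient's earlier way of taking inhaled drugs is therefore an obvious candidate predictor of the device prescribed. The cohort deliberately includes prior users of other inhalers, so this history varies between patients.

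Nebuliser use matters most. It may mark more advanced disease, which Table 1 cannot capture through lung function, and it may mark trouble with hand-held inhalers. It could thus relate both to device choice and to the two primary outcomes, exacerbation and pneumonia hospitalization. If it differs between arms after weighting, both primary hazard ratios carry that difference. A balance assessment limited to the listed covariates would not show it.

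**Working it through.** **Step 1: is delivery form in the model under another name?** The two statements of the adjustment set both point to Table 1. Reading all of its variables finds none that separates nebulised from hand-held use, or one hand-held device from another. Appendix Table 3, which is not available here, is described as supplying codes for the named variables. There are two possibilities:

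- If its SABA list includes nebuliser solutions, nebulised and hand-held fills are pooled in one variable.
- If it excludes them, nebulised use does not appear at all.

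Either way, nebuliser use is not a separate covariate.

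**Step 2: would another planned analysis reveal it?** The balance metrics in the Statistical analysis section describe main effects and higher-order terms, with no metric for covariates outside Table 1. Sensitivity analyses, row 10 (high-dimensional propensity score matching) might select delivery form empirically. It names no such variable and does not alter the primary estimate. It also replaces weighting with matching, so a shift in the estimate could not be attributed to delivery form.

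**Step 3: how large could it be?** The Protocol gives no figure to reproduce: no nebuliser prevalence, event rate or effect size. The following inputs are all assumptions, used only for scale:

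- p0 = 0.20: nebuliser use in one arm after weighting.
- p1 = 0.25, 0.30 or 0.40: nebuliser use in the other arm after weighting.
- r = 1.3, 1.5 or 2.0: hazard ratio for nebuliser use that remains after the Table 1 covariates are balanced.

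The standard formula for one omitted binary confounder gives the apparent hazard ratio when the devices do not differ, treating the hazard ratio as a rate ratio:

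apparent HR = [1 + p1(r − 1)] / [1 + p0(r − 1)]

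| r | p1 = 0.25 | p1 = 0.30 | p1 = 0.40 |
| --- | --- | --- | --- |
| 1.3 | 1.075/1.06 = 1.014 | 1.09/1.06 = 1.028 | 1.12/1.06 = 1.057 |
| 1.5 | 1.125/1.10 = 1.023 | 1.15/1.10 = 1.045 | 1.20/1.10 = 1.091 |
| 2.0 | 1.25/1.20 = 1.042 | 1.30/1.20 = 1.083 | 1.40/1.20 = 1.167 |

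The middle case is 1.045 and the range is 1.014 to 1.167. The Protocol does not say which arm would hold more nebuliser users. If it were the referent arm, the factors invert: 1.10/1.15 = 0.957 in the middle case, with a range from 1.20/1.40 = 0.857 to 1.06/1.075 = 0.986.

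**The case against.** The strongest reply is that Table 1 already covers much of this ground. It holds baseline and recent exacerbations, short-acting fills, home oxygen, CPAP/BiPAP, chronic prednisone, roflumilast, chronic azithromycin, pulmonologist visits and prescriber, admissions and readmissions, age, "Frailty score" and dementia or other neurologic disease. These may absorb a good part of what nebuliser use would add. That stands, but how much they absorb is unknown, because balance on nebuliser use is never examined.

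A reader might infer that the main drivers of device choice are left unbalanced. The Protocol does not support this. It does not say what drives the choice, and it reports nothing on nebuliser use by arm. The remark in Part 1 about handling errors does not help either. It describes what may happen once a device is in use, which is part of the effect being estimated and not evidence of selection at baseline.

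A second fair reply is that delivery-form variables do not all play the same role. Prior metered-dose or dry powder use may mainly predict the next device, with little separate path to the outcome. Forcing such a near-instrument into the weights can inflate their variability and amplify any residual confounding. The team chose its method partly to avoid extreme weights. This stands, and it limits what should go into the primary model.

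The high-dimensional score is a systematic, data-driven selection, so it is a relevant robustness check. It still does not correct the primary hazard ratio.

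**Conclusion.** The point holds in a limited form. In a same-drug device comparison that admits prior inhaler users, the primary model neither adjusts for baseline nebuliser use nor checks its balance. Bias is possible but not shown. The illustrative 1.01 to 1.17 rests wholly on assumed inputs, and the upper end needs both a 20-point imbalance left after weighting and a residual hazard ratio of 2.0. The effect may be negligible. It could matter if the true hazard ratio is close to 1, and Part 1 cites a small trial that found similar efficacy for the two products. The change is worth making because it is specific and inexpensive. The point does not extend to putting every prior-device variable into the primary weights.

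**What to change.** **Primary model.** In Table 1, split SABA, SAMA and SAMA-SABA fills into nebulised and hand-held forms, and add a nebuliser-equipment claim. Include these in the primary CBPS model. Re-estimate the weights and rerun the balance table before outcomes are analysed.

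**Balance reporting only.** For prior controller device type (metered-dose or dry powder) and for spacer claims before day 0, report standardised differences after weighting, and adjust for them only in a sensitivity analysis. Spacer claims should stop before day 0 because a spacer dispensed with the index inhaler is part of the exposure.

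**Cost.** This adds a few covariates, formulation-level code lists, a rerun balance table and possibly slightly more variable weights. The plan already uses claims of this kind: the exposure is defined by device-specific product, and home oxygen by equipment claims. Sparse nebulised categories, such as SAMA or SAMA-SABA, can be collapsed.

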Moderate COPD exacerbations are defined as requiring prednisone for 5-14 days, and severe COPD exacerbations are defined as requiring hospitalization (with COPD in the primary position). The full codes for moderate exacerbations, severe exacerbations, and moderate or severe exacerbations are below. Defining moderate exacerbations based on prednisone fills (of 5-14 days) has been validated with PPV of 0.73 (0.70-0.77).^3^ Note that, on sensitivity analysis, we will require both a prednisone and an antibiotic fill (PPV 0.80 [95% CI 0.74-0.86]).^3^ Defining severe COPD exacerbations based on COPD diagnosis codes in the primary position has been validated with a PPV of 0.86.^4^

The primary analysis is time to first moderate or severe COPD exacerbation. In secondary analyses (see below), we will analyze cumulative exacerbations during one year of follow up using a Prenctice, Williams, and Peterson Total Time Model. We will require that distinct episodes of exacerbation be separated by at least 14 days. Therefore, if a patient meets the criteria for an exacerbation more than once within 14 days, this will be counted as 1 unique episode that begins at the first exacerbation within the episode.

Episodes that meet both moderate and severe exacerbation criteria within 14 days of each other will be counted as 1 severe exacerbation that begins at the time of meeting the criteria for the first exacerbation within the episode, regardless of whether the criteria are for a moderate or severe exacerbation.

Therefore, there are 2 types of prednisone fills that would otherwise meet criteria for moderate exacerbations but are instead grouped as severe COPD exacerbations: (1) First, prednisone fills that occurred within 14 days AFTER the end of a COPD hospitalization will count as a severe COPD exacerbation beginning with the start of the COPD hospitalization. The prednisone script is likely just completing the therapy that was begun in the hospital and so should not count as a new exacerbation. (2) Second, prednisone scripts that occurred within 14 days BEFORE the start of a COPD hospitalization will count as a severe COPD exacerbation beginning with the start of the prednisone script. When prednisone is not enough and hospitalization is required, this episode is a severe exacerbation.

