**Primary safety outcome: First hospitalization for pneumonia**

We will allow a pneumonia diagnosis in any position in our prior work since this is an acute condition (and we can be confident that, if somebody has a pneumonia diagnosis during a hospitalization, he/she is experiencing an acute process—which stands in contrast to a COPD diagnosis in any position during the hospitalization, where we cannot be sure that this is an acute process). The full codes for pneumonia hospitalizations are below and have been validated with a PPV of 0.88 (95% CI 0.82-0.92)^5^ using ICD-9 codes. We converted ICD-9 codes to ICD-10 codes using clinical review, because our study period was after the transition to using ICD-10 codes in the United States.

This event measure was defined as occurring when any of the following criteria were met:

- The occurrence of **Inpatient Confinement** with the following attributes:
  - **Diagnosis Code (Any Confinement Position), ICD-9** is any of: { “480”, “480.0”, “480.1”, “480.2”, “480.3”, “480.8”, “480.9”, “481”, “482”, “482.0”, “482.1”, “482.2”, “482.3”, “482.30”, “482.31”, “482.32”, “482.39”, “482.4”, “482.40”, “482.41”, “482.42”, “482.49”, “482.8”, “482.81”, “482.82”, “482.83”, “482.84”, “482.89”, “482.9”, “483”, “483.0”, “483.1”, “483.8”, “484”, “484.1”, “484.3”, “484.5”, “484.6”, “484.7”, “484.8”, “485”, “486”, “487.0”, “488.01”, “488.11”, “488.81” }
    - 480 - VIRAL PNEUMONIA
    - 480.0 - PNEUMONIA DUE TO ADENOVIRUS
    - 480.1 - PNEUMONIA DUE TO RESPIRATORY SYNCYTIAL VIRUS
    - 480.2 - PNEUMONIA DUE TO PARAINFLUENZA VIRUS
    - 480.3 - PNEUMONIA DUE TO SARS-ASSOCIATED CORONAVIRUS
    - 480.8 - PNEUMONIA DUE TO OTHER VIRUS NOT ELSEWHERE CLASSIFIED
    - 480.9 - VIRAL PNEUMONIA UNSPECIFIED
    - 481 - PNEUMOCOCCAL PNEUMONIA [STREPTOCOCCUS PNEUMONIAE PNEUMONIA]
    - 482 - OTHER BACTERIAL PNEUMONIA
    - 482.0 - PNEUMONIA DUE TO KLEBSIELLA PNEUMONIAE
    - 482.1 - PNEUMONIA DUE TO PSEUDOMONAS
    - 482.2 - PNEUMONIA DUE TO HEMOPHILUS INFLUENZAE (H. INFLUENZAE)
    - 482.3 - PNEUMONIA DUE TO STREPTOCOCCUS
    - 482.30 - PNEUMONIA DUE TO STREPTOCOCCUS UNSPECIFIED
    - 482.31 - PNEUMONIA DUE TO STREPTOCOCCUS GROUP A
    - 482.32 - PNEUMONIA DUE TO STREPTOCOCCUS GROUP B
    - 482.39 - PNEUMONIA DUE TO OTHER STREPTOCOCCUS
    - 482.4 - PNEUMONIA DUE TO STAPHYLOCOCCUS
    - 482.40 - PNEUMONIA DUE TO STAPHYLOCOCCUS UNSPECIFIED
    - 482.41 - METHICILLIN SUSCEPTIBLE PNEUMONIA DUE TO STAPHYLOCOCCUS AUREUS

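### Table 1, which fixes the propensity model, covers other chronic lung disease (asthma apart), steroid-treated inflammatory disease and immunosuppression only through partial proxies; a few named covariates would close the gap cheaply

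*Protocol*

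**What the plan says.** **Adjustment set.** The Covariates section says of Table 1: "All variables listed below will be included in our propensity score model". The Statistical analysis section repeats this for the covariate balancing propensity score (CBPS), whose logistic model is specified "including the variables in Table 1 as predictors of exposure". Appendix Table 3 is described as holding the codes for the variables named in Table 1.

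**What Table 1 names.** Asthma is the only chronic lung disease entered as a diagnosis. Related entries are:
- baseline moderate and severe exacerbations and pneumonia hospitalizations;
- respiratory antibiotic fills and chronic prednisone;
- GERD, dementia or other neurologic disease, and both malignancy groups;
- a combined comorbidity index and a frailty score;
- CT scan, bronchoscopy, pulmonologist visits and influenza vaccination.

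Asthma is read over all available data. The other diagnoses are read over 180 days.

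**Outcome and cohort.** Section 8.1.A builds the moderate exacerbation from a continuous prednisone episode without a nearby COPD admission. The displayed sequence contains no respiratory diagnosis. The definition based on prednisone fills "has been validated with PPV of 0.73 (0.70-0.77". Cohort entry needs three outpatient COPD claims or one inpatient claim, and age 40 or over. Part 1 (Background) states that Diskus is approved for COPD and asthma, and HFA for asthma only.

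**The concern.** Table 1 has no named entry for bronchiectasis, interstitial lung disease or sarcoidosis; for inflammatory arthritis, polymyalgia, gout or inflammatory bowel disease; for immunosuppressive drugs beyond chronic prednisone; or for pneumococcal vaccination. Dysphagia and aspiration are not named either.

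A short prednisone course given for one of the inflammatory conditions can be recorded as a moderate exacerbation. Other lung disease and immunosuppression can raise the risk of a pneumonia admission. If such conditions are more frequent among users of one device, the primary hazard ratios carry that difference whichever device works better.

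The HFA label makes a difference by device conceivable, because the choice of HFA may follow the prescriber's view of the underlying airway disease. Of the alternative airway diagnoses, only asthma is balanced by name. Good balance on Table 1 would not reveal a remaining difference, since these conditions are not tabulated. The study compares one drug combination in two devices, and the Background cites a small trial with similar efficacy, so even a modest shift could affect the reading of a result near 1.

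**Working it through.** The Protocol states no event count, power or prevalence by device, so there is no planned figure to reproduce. Three checks apply.

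**1. Can an unrelated prednisone course count as an event?** As displayed in section 8.1.A, yes. The conditions are a prednisone episode after cohort entry and no COPD hospitalization from 14 days before it starts to 14 days after it ends. Sensitivity analysis 5(a) adds an office or ED visit before the fill, which confirms that the main definition does not ask for one. The code behind the underlying prednisone-fill measure is not printed.

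**2. How large could the bias be?** For an omitted binary condition with prevalence p1 (HFA) and p0 (Diskus) and rate ratio RR for the outcome:

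bias factor = [1 + p1(RR − 1)] / [1 + p0(RR − 1)]

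All inputs are assumptions, since the documents give none.

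| p1 | p0 | RR | Calculation | Factor |
|---|---|---|---|---|
| 0.06 | 0.05 | 2 | 1.06/1.05 | 1.010 |
| 0.08 | 0.05 | 2 | 1.08/1.05 | 1.029 |
| 0.10 | 0.05 | 2 | 1.10/1.05 | 1.048 |
| 0.08 | 0.05 | 3 | 1.16/1.10 | 1.055 |
| 0.10 | 0.05 | 3 | 1.20/1.10 | 1.091 |

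With equal prevalence the factor is 1. Swapping the arms inverts it, so the direction is unknown. The formula treats the condition as unrelated to everything in Table 1. Weighting on correlated proxies would bring the factor closer to 1.

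**3. Do the stated positive predictive values (PPVs) add to this?** Unconfirmed shares are 1 − 0.73 = 27% for moderate events (23% to 30% from the interval), 1 − 0.86 = 14% for severe events and 1 − 0.88 = 12% for pneumonia (8% to 18%). Let f be the ratio of false-positive event rates between arms, with the PPV applying to the Diskus arm:

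observed RR = PPV × true RR + (1 − PPV) × f

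- f = 1, PPV 0.73: a true RR of 0.80 is seen as 0.73 × 0.80 + 0.27 = 0.854. A true RR of 1 stays at 1.
- f = 1.2 (assumed), PPV 0.73, true RR 1: 0.73 + 0.27 × 1.2 = 1.054.
- f = 1.2 (assumed), PPV 0.88, true RR 1: 0.88 + 0.12 × 1.2 = 1.024.

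Equal false-positive rates only pull the estimate towards 1. A spurious difference needs f to depart from 1, and the PPVs say nothing about f.

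**The case against.** **No imbalance is shown.** Confounding needs these conditions to differ between users of the two devices after weighting on all of Table 1. The documents contain no data on that. This objection stands, and it limits the point to a precaution.

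**Much is already covered.** Baseline moderate exacerbations are themselves defined by prednisone, so they carry recent courses whatever the cause. Chronic prednisone, malignancy, GERD, neurologic disease and baseline pneumonia admissions reach part of the rest. The components of the comorbidity index and the frailty score are not shown and may reach more. This also stands. A reader might infer that Table 1 covers none of the conditions behind non-COPD prednisone or pneumonia; asthma and these proxies refute that. What remains is that a summary score need not balance its components, and that most proxies look back only 180 days.

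**Sensitivity analyses help.** The high-dimensional propensity score run uses hundreds of empirically defined covariates, and other runs tighten the moderate-event and pneumonia definitions. But the high-dimensional run is matched, whereas the primary analysis is weighted for the average treatment effect. A discrepancy could reflect the estimand as well as the covariates, so it does not replace a fuller primary model. The logistic and entropy-weighting runs are not described as adding covariates.

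**The PPVs.** A reader might infer that they show a sizeable share of events arising outside COPD. They do not. The pneumonia codes "have been validated with a PPV of 0.88 (95% CI 0.82-0.92", but that concerns whether pneumonia was present; a pneumonia caused by immunosuppression is still a true positive. The 27% for moderate events does not identify the cause of the unconfirmed ones. By its title in the reference list, the cited validation comes from UK primary care records rather than US claims.

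**Other safeguards.** A reader might also take the age limit as the only guard against other respiratory disease. The COPD claims requirement applies as well, and section 6.1 presents age as a further aid.

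**Conclusion.** The point holds in a limited form. The primary propensity model is tied to a list that lacks specific entries for non-asthma chronic lung disease, steroid-treated inflammatory disease, immunosuppressive drugs and pneumococcal vaccination. The prednisone-only definition of the moderate event and the asthma-only label of HFA make outcome-related imbalance plausible. It is not demonstrated.

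The likely size is small: a factor of about 1.01 to 1.09 on the hazard ratio, in either direction. This assumes prevalences of 6% to 10% against 5%, rate ratios of 2 to 3, and no correlation with Table 1. The true residual could be smaller because of the proxies. The reading that the primary results would be biased goes beyond the documents. This is a low-cost improvement to the primary model.

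**What to change.** Before outcomes are analysed, add to Table 1, and so to the CBPS model:
- bronchiectasis;
- interstitial lung disease or sarcoidosis;
- inflammatory arthritis or polymyalgia;
- gout;
- inflammatory bowel disease;
- immunosuppressive drugs;
- pneumococcal vaccination.

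Dysphagia or aspiration is optional, since the pneumonia code list shows no aspiration-specific code. Consider reading the chronic diagnoses and the vaccination over all available data, as already done for asthma. Re-fit the weights, repeat the balance comparison behind the choice of CBPS, and report the standardized mean differences of the added items before and after weighting. Small unweighted differences would largely settle the concern.

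The cost is about seven code lists and one re-fit, possibly a slightly lower effective sample size, and look-back that varies between patients if all available data are used.
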